### 2.3. Sample Size Estimation

The sample size was estimated based on previous literature and the ANCOVA to analyse the differences between and within groups [40]. A sample size calculation was conducted using G*Power 3.1.3 (Universität Düsseldorf, Düsseldorf, Germany) [41]. We predicted the inclusion of 25 participants per group, a total of at least 100 community-dwelling older adults, both men and women, considering a moderate effect size of 0.40, an alpha-risk of 0.05, and a beta-risk of 0.20 in a 2-sided test, and anticipating a 20% dropout rate.

### 2.4. Ethics Approval and Data Management 

The study protocol was approved by the Ethical Committee of the Faculty of Food and Nutrition Sciences of the University of Porto (reference 17/2021/CEFCNAUP/2021), the Ethics Committee of Northern Region Health Administration (report CE/2022/71), and the Data Protection Unit of the University of Porto. The project procedures followed all the ethical standards and the 1964 Helsinki Declaration. 

Before data collection, the principal researcher obtained informed consent from interested participants. 

Data coding, security, and storage procedures followed the guidelines of the Data Protection Unit of the University of Porto. Information regarding confidentiality and the transfer of data obtained within the scope of the MED-E project is present in the study information document for participants, attached to the informed consent. Data confidentiality and anonymity were guaranteed in all phases of the study.

### 2.5. Study Intervention

#### 2.5.1. Sustainable Healthy Diet Group (SHD) 

Diet intervention lasted approximately three months. Participants were provided, weekly, with an SHD food supply, including planted-based foods (nuts and pulses), olive oil, and oily fish, which might have contributed to higher compliance with the overall dietary pattern. Based on the Mediterranean Diet and the latest EAT-Lancet recommendations [12], the individual food supply included per week 125 g of nuts (walnuts, considering a daily serving of 25 g); 350 g of dry pulses (chickpeas and different types of beans, based on a daily serving of 50 g); 280 g of olive oil (a bottle of olive oil was delivered per month); and two servings of oily fish (sardine fillets and tuna, 100 g servings). 

Additionally, the intervention included a total of four sessions: three group sessions (including an SHD culinary workshop) and one telephone interview ranging from 30 (the individual session) to 60 min with a trained nutritionist at the beginning, 1-month, 2-months, and 2.5-months into the intervention. The group and individual sessions were held by nutritionists. The focus was on acquiring knowledge and maximising individual participation. Group sessions involved a maximum of 25 participants. All the sessions were held emphasising participants’ involvement to allow for more dynamic and interactive meetings.

The first group session was an introductory one explaining the principles of an SHD and the benefits of this pattern in several health outcomes. The participants learned how to evaluate environmental impact, and some examples of food footprints were given. The recommended serving sizes of an SHD and the seasonal foods for each month were also presented. 

The second group session was an SHD culinary workshop in an experimental kitchen laboratory of Faculty of Nutrition and Food Sciences (FCNAUP) to increase participants’ knowledge, skills, and literacy regarding SHD recipes. In this SHD culinary workshop, seasonal and Mediterranean-based local food products were chosen. Participants were organised into four groups, and each was required to elaborate on recipes. The participants tasted all the recipes at the end of the SHD culinary workshop. The workshop included as recipes (i) a soup with a traditional and local Portuguese green kale named Caldo Verde; (ii) a cold Mediterranean mackerel salad with pulses; (iii) roasted mackerel with potatoes and seasonal vegetables (onion, garlic, different colour peppers, broccoli, and carrots); (iv) and sardines rice with turnips and greens. Dessert included seasonal fresh fruits and walnuts.

The third group session included tips on supermarket shopping and food storage and a novel approach to tackling food waste to capacitate the participants to choose fresher, healthier, traditional, seasonal, and cheap products. Participants learned how to promote sustainability during culinary activities. Sustainable and healthy weekly meal plans and cooking recipes were provided. 

In individual interviews, food and nutritional education considered baseline dietary intake and nutritional adequacy assessments, and recommendations in line with the latest EAT-Lancet recommendations for adopting an SHD were set [12].

#### 2.5.2. Multicomponent Training Group (MT) 

The MT exercise program included 50-min group sessions three times a week on non-consecutive days. The sessions were distributed into three main parts: 8–10 min of warm-up (including walking, postural, mobility, and stretching exercises), 30–35 min of specific training (including balance, coordination, strength, and aerobic conditioning), and 5 min cooldown (breathing and stretching exercises). Exercise prescription followed the main guidelines from the American College of Sports Medicine [42] and the World Health Organization (WHO) [43]—60–80% of maximum heart rate (HRmax) and 50–70% of one-repetition maximum (1RM). 

Simple, age-adapted, enjoyable, and functional exercises were preferred. Before the training program, a two-month adaptation period was implemented to familiarise the participants with the activities, observe their individual physical needs and promote socialisation among them. The adaptation period maintained a low-intensity range of 40 to 50% HRmax in the aerobic exercises and one set of 12–15 slow repetitions for the strength exercises. The focus was on learning the movements. Exercise intervention prescription, implementation, and evaluation were performed by elderly specialist exercise professionals. Sessions involving a maximum of 25 participants were held in appropriate, safe gymnasiums. Whenever possible, sessions were accompanied by music to promote participants’ involvement and enthusiasm and confer intensity. Balance exercises gradually reduced the base of support and/or reduced sensory input, and included dynamic movements that perturbed the centre of gravity. Additional focus was placed on some easy coordination exercises and conscious control of the body. Four to six multi-joint strength exercises involving major muscle groups were included in each session. The number of repetitions gradually decreased (12–15 to 10–12), but the load increased and could be lifted correctly to volitional fatigue. A rest period was completed between sets. Aerobic endurance was achieved with low-impact exercises, gradually increasing intensity, duration, and HR. The Rated Perceived Exertion (RPE) scale was used to support the exercise intensity control—as medication induces HR alterations and adverse events (such as pain or fatigue). The number of falls was recorded at the end of each MT session. Session attendance was recorded [44] and participants missing more than 12 consecutive sessions (equivalent to one month of detraining) were excluded from the final analyses.

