## 2. Design and Methods

The study was designed as a quasi-experimental, 12-week, four-armed, diet and exercise intervention with community-dwelling elderly residents from Porto, Portugal (Figure 1). This protocol report follows the Standard Protocol Items: Recommendations for Interventional Studies (SPIRIT) 2013 checklist [32]. 

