### 2.2. Eligibility and Recruitment

This study included individuals (i) aged 65 years or older, (ii) living in the community, (iii) with independent mobility, (iv) with no past medical history of neuropsychiatric conditions (e.g., major depression or bipolar disease), and (v) with no musculoskeletal or cardiovascular disorders that contraindicate participation in moderate exercise and testing. The exclusion criteria included individuals engaged in regular moderate to vigorous exercise training and followed by a nutritionist.

Eligible participants received a complete explanation of the study’s purposes, risks, and procedures. Before data collection, the principal researcher obtained informed consent from interested participants. After the agreement, participants were assigned into a 3-month SHD, MT, combined SHD and MT (SHD + MT), or control group (CG). 

Participants were assessed at baseline and after 3 months of intervention. At baseline, sociodemographic and economic, lifestyle (e.g., tobacco use and habitual physical activity), and general clinical data were collected through a structured questionnaire. Possible changes in these data were assessed in post-intervention assessments. At these two time points, nutritional and food intake evaluations were obtained through multiple reliable tools [33,34,35]: the Mini Nutritional Assessment [36]; physical capacity assessments through the Senior Fitness Test [37] and handgrip strength; a whole-body Dual X-ray absorptiometry (QDR 4500/A, Hologic Explorer, version 12.4, Bedford, MA, USA); a Montreal Cognitive Assessment [38]; the Quality of Life for Old Module (WHOQOL-OLD) [39]; and accelerometry (ActiGraph GT9X Link, Manufacturing Technology, Inc., South Bend, IN, USA) were performed. 

Participants were only informed about which group they belonged to after baseline assessments. Well-trained and skilled researchers executed the same procedures during the two assessment periods.

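### A two-month exercise adaptation period does not fit a uniform 3-month comparison; read literally, the exercise arms run about 5 months from baseline to post-test and the other arms about 3

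*Protocol article*

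**What the plan says.** All references are to the protocol article.

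- **Overall length.** Section 2 describes a "quasi-experimental, 12-week, four-armed, diet and exercise intervention". The Abstract and section 2.2 likewise give every arm a length of three months.
- **Assessments.** Section 2.2: "Participants were assessed at baseline and after 3 months of intervention". Section 2.6.1 has blood for the primary outcome drawn at these two points only.
- **Disclosure.** Section 2.2: "Participants were only informed about which group they belonged to after baseline assessments".
- **Adaptation.** Section 2.5.2, on the exercise arm: "Before the training program, a two-month adaptation period was implemented to familiarise the participants with the activities". Its content was exercise: "The adaptation period maintained a low-intensity range of 40 to 50% HRmax in the aerobic exercises and one set of 12–15 slow repetitions".
- **Main programme.** Section 2.5.2: "The MT exercise program included 50-min group sessions three times a week on non-consecutive days", prescribed at 60–80% of HRmax.
- **Other arms.** Section 2.5.1 gives the diet intervention about three months. Section 2.5.4 gives the control group one nutrition session and two low-intensity activity sessions. Neither mentions a run-in or a wait. Section 2.5.3 gives SHD+MT the same two interventions, but not when its diet began relative to adaptation.

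**The concern.** The primary outcomes are pre-to-post changes in blood biomarkers and metabolic profile. Section 2.7 analyses them with a percentage change and a repeated-measures ANOVA. That analysis treats the baseline-to-post interval as the same in every arm and baseline as untreated. A two-month exercise period that belongs only to the exercise arms puts one or the other in doubt, or else reduces the training actually given at the stated intensity.

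If the interval differs by arm, elapsed time coincides with being in an exercise arm, and no covariate can separate the two. Allocation was not randomised, so nothing else in the design protects the contrast. If baseline came after adaptation, the exercise estimates start from people who had already trained for two months, and the baseline physical-activity measurement intended as a confounder (section 2.6.3) would be affected too. In either case the result could not be reported simply as the effect of a 3-month exercise programme.

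**Working it through.** **Inputs.** Main programme: 12 weeks (section 2) or 3 months (section 2.2). Adaptation: 2 months (section 2.5.2). Frequency: 3 sessions a week (section 2.5.2). One month = 365.25 / 12 / 7 = 4.35 weeks.

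**The plan's own figure.** 3 × 4.35 = 13.0 weeks, against a stated 12 weeks. The two descriptions agree to within about a week, and the diet is given only as approximately three months. Without the adaptation period there is no conflict.

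**Placement A: baseline, disclosure, adaptation, programme, post-test.** This follows the wording most directly.
- MT and SHD+MT: 2 + 3 = 5 months. In weeks, 8.7 + 12 = 20.7, or 5 × 4.35 = 21.7 with a 3-month programme.
- SHD and CG: 3 months (12 to 13 weeks), if they had no matching wait.
- Ratio: 5 / 3 = 1.67, a 67% longer interval in two of the four arms.
- Exercise exposure between the two blood samples: 5 months, not 3.

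Four arms give 4 × 3 / 2 = 6 pairwise contrasts:

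| Contrast | Intervals (months) |
|---|---|
| MT vs CG | 5 vs 3 |
| MT vs SHD | 5 vs 3 |
| SHD+MT vs CG | 5 vs 3 |
| SHD+MT vs SHD | 5 vs 3 |
| SHD vs CG | 3 vs 3 |
| SHD+MT vs MT | 5 vs 5 |

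Four contrasts have unequal intervals. Of the two with equal intervals, only SHD vs CG covers 3 months.

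**Placement B: adaptation, baseline, programme, post-test.** The interval is 3 months in every arm. But people attending two months of exercise sessions would know before baseline that they were in an exercise arm, which conflicts with the disclosure statement in section 2.2. Their baseline would follow about 8 to 9 weeks of low-intensity training.

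**Placement C: adaptation inside the 12 weeks.** The interval is again equal, but this conflicts with the statement that adaptation came before the programme.
- Adaptation takes 8 to 8.7 of 12 weeks, a share of 8 / 12 = 67% to 8.7 / 12 = 72%.
- Remaining at the prescribed intensity: 12 − 8 = 4 weeks, or 12 − 8.7 = 3.3 weeks.
- In sessions, assuming three a week throughout: 12, or about 10, of 36.

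**Result.** A keeps the wording of sections 2, 2.2 and 2.5.2 only if the 12 weeks count the main programme alone, and it then yields unequal intervals. B and C equalise the intervals, but each contradicts a sentence in the text.

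**The case against.** The best defence is that the passages can be made to agree. Section 2 attaches the 12 weeks to the intervention, and section 2.2 times the second assessment after three months of intervention, not three months after baseline. On that reading placement A contradicts nothing. This stands: a reader might infer that the statements are mutually impossible, and the text does not support that. But the reading that rescues the wording is the one that produces the 5-versus-3-month intervals.

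A reader might also infer that the exercise arms must have either a 5-month interval or a trained baseline. That is too strong as well. Under placement C neither holds, and an equal two-month wait in SHD and CG would equalise the intervals under placement A. No such wait is described, but it cannot be ruled out. The 67% figure is therefore conditional.

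A seasonal difference between arms is a further tempting inference. Section 2.1 gives only the overall collection window, November 2021 to December 2022, with no dates by arm, so such a difference is possible but not shown.

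Finally, Figure 1 is the study flow-chart and is not shown, and the full protocol may fix the order. That limits how firmly any one placement can be asserted. It does not turn the point into a mere omission: the article itself states the adaptation's length, content and position, and an analysis plan cannot change when blood was drawn.

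**Conclusion.** The point holds in a conditional form. Taken literally, the text gives about 5 months (20.7 to 21.7 weeks) from baseline to post-test in MT and SHD+MT, and about 3 months (12 to 13 weeks) in SHD and CG. Four of six pairwise contrasts then mix exercise with elapsed time and reflect 5 months of exercise. This rests on two assumptions that the text does not confirm: that baseline preceded adaptation, and that SHD and CG had no equal wait.

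The alternatives do not remove the problem. One conflicts with disclosure after baseline and gives a partly trained baseline. The other conflicts with the stated position of the adaptation and leaves about 3.3 to 4 weeks at the prescribed intensity. An equal unstated wait would cure the inequality between arms, but the exercise estimates would still cover 5 months. The timing has to be settled before the exercise results can be called 3-month effects.

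**What to change.** Reconcile section 2, section 2.2 and section 2.5.2 (both its programme and its adaptation paragraphs). Which schedule is right is for the investigators to state from their records; none is proposed here.

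1. State where the baseline assessment fell relative to adaptation, whether adaptation counts towards the three months, and whether SHD and CG waited.
2. State when the diet began in SHD+MT relative to adaptation.
3. Tabulate, by arm, the actual days from baseline to post-test and the calendar dates of both assessments.
4. If the intervals differ, describe the four exercise-versus-no-exercise contrasts as effects of the whole adaptation-plus-training period with unequal follow-up. Treat only SHD vs CG as a 3-month contrast. Describe SHD+MT vs MT as an equal-interval contrast over about 5 months; although its intervals match, it should not be reported as a 3-month result.
5. If baseline followed adaptation, correct the disclosure statement and describe the exercise estimates as changes beyond an already trained baseline.

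The cost is a text correction and a table from dates that should already be on record, since data collection ended in December 2022. The downside is narrower exercise claims.

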### 2.7. Statistical Analyses

Descriptive results will be expressed as median and inter-quartile range (IQR) or mean and standard deviation (SD), as appropriate, for continuous variables. Discrete variables will be presented as counts and percentages. The minimum threshold value for statistical significance used will be *p* ≤ 0.05.

The normality tests, histogram, and plot distribution will assess the normality of data distribution. Comparative analyses between participants and dropouts will be realised by *t*-test or Mann–Whitney U-test for continuous variables and Pearson-Chi Squared or Fisher exact test for categorical variables to determine whether attrition bias was observed. 

Potential differences among intervention groups in baseline measurements will be evaluated using a one-way Analysis of Variance (ANOVA) or correspondent non-parametric Kruskal-Wallis test. A Pearson Chi-squared or Fisher exact test will be used for between-group comparisons of categorical variables. 

Covariates (e.g., sociodemographic and economic characteristics; clinical history, such as the presence of comorbidities; and daily physical activity) were selected a priori and tested. The confounding variables will be entered as covariates in the ANOVA models. For each model, the contribution of all covariates will be tested separately; only the ones that change the magnitude of the association by at least 10% will be included in the final models. The fit of the models will be determined. Whenever necessary, we will use weighted samples to tackle the bias imposed by differential sampling probabilities.

A delta percentage will be calculated to assess the percentage of change between baseline and post-intervention assessments. An ANOVA or correspondent non-parametric test with repeated measures will be performed for differences in main effects and interactions for each dependent variable. When significant interactions are found, Bonferroni posthoc tests will determine the origin of the differences. Multivariable regression analyses will explore the associations between blood-based markers and metabolomics and the secondary outcomes.

Geographical information systems data will be collected. The associations of the primary and secondary outcomes with environmental features will be explored through generalised linear models to understand whether built environment food and PA features lead to statistically significant differences in participants’ dietary and exercise routines.

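### Training, and to a lesser degree the diet sessions, are delivered in groups of up to 25, but the sample size and the repeated-measures ANOVA treat participants as independent, so 5% false positives and 80% power are not assured

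*Protocol article*

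**What the plan says.** **Delivery.** Section 2.5.2 describes 50-minute group training three times a week and caps the classes: "Sessions involving a maximum of 25 participants were held in appropriate, safe gymnasiums". Section 2.5.1 gives three nutrition group sessions, one of them a cooking workshop, with the same cap: "Group sessions involved a maximum of 25 participants". The diet arm also has individual parts: a weekly food supply and one telephone interview. The combined arm (2.5.3) receives both programmes. Controls (2.5.4) were offered one nutrition session and two light activity sessions, plus weekly telephone contact.

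**Sample size.** Section 2.3 states "The sample size was estimated based on previous literature and the ANCOVA to analyse the differences between and within groups". Its inputs are given as "considering a moderate effect size of 0.40, an alpha-risk of 0.05, and a beta-risk of 0.20 in a 2-sided test", "anticipating a 20% dropout rate", and the result is "We predicted the inclusion of 25 participants per group, a total of at least 100 community-dwelling older adults". No ICC or design effect appears.

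**Analysis.** Section 2.7 plans: "An ANOVA or correspondent non-parametric test with repeated measures will be performed for differences in main effects and interactions for each dependent variable". The covariates it lists are participant characteristics. Class, instructor and site are not among them. The article does not label this ANOVA primary, but because it applies to every dependent variable it covers the primary blood biomarkers.

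**The concern.** People in one class share an instructor, peers, pace and venue, so their changes from baseline may be correlated. Section 2.5.2 encourages this: the adaptation period is partly meant to build social contact among participants, and music is used to raise involvement and intensity. The repeated-measures structure handles two visits by one person. It does not handle correlation between classmates. The weighting mentioned in 2.7 concerns sampling probabilities, which is a different matter.

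With positive class correlation, an arm mean varies by chance more than the spread between individuals suggests. The ANOVA takes its error term from that individual spread, so chance differences between classes can be read as intervention effects, for each biomarker tested. This is a standard-error problem. It would remain even if the arms were perfectly balanced on site and recruitment source.

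The class cap (25) equals the planned arm size (25), so an arm could be a single class. Class and arm would then be inseparable.

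**Working it through.** **Inputs from the article.** Four arms; 25 per arm; 20% dropout, so 25 x 0.80 = 20 analysed per arm and 80 in total; effect size 0.40, read as Cohen's f (the ANCOVA metric in G*Power); alpha 0.05; power 0.80; class cap 25.

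**Assumed, because the article gives no figure.** ICC of the change score 0.01 to 0.10; one, two or four equal classes per active arm (20, 10 or 5 analysed per class); separate classes for each arm; control arm unclustered.

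**Step 1: the plan's own figure.** Under independence the noncentrality is f² x N, with 3 numerator df. The smallest N with 80% power is 73, hence 19 per arm. With dropout, 19 / 0.80 = 23.75, or 24 per arm. The stated 25 is reproduced to within one participant and is slightly generous. With N = 80 the noncentrality is 0.16 x 80 = 12.8 and the power is 84.5% (df 3 and 75).

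**Step 2: design effect.** DE = 1 + (m - 1) x ICC, and the standard error of an arm mean grows by √DE. At ICC 0.05:
- m = 20: 1 + 19 x 0.05 = 1.95, √ = 1.40
- m = 10: 1 + 9 x 0.05 = 1.45, √ = 1.20
- m = 5: 1 + 4 x 0.05 = 1.20, √ = 1.10

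**Step 3: simulation.** Change scores with total variance 1 and 20 per arm were analysed by one-way ANOVA against F(0.95; 3, 76). With two time points this is the group-by-time test. For power, the control mean is low, the single interventions are in the middle and the combined arm is high, at f = 0.40. The last column uses the critical value that restores 5% size. That treats the ICC as known, so it is an upper bound. Independent runs agree to about one point.

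| ICC | Classes per active arm | False positives, planned ANOVA | Power of a test held at 5% |
|---|---|---|---|
| 0 | any | 5% | 85% |
| 0.01 | 1 / 2 / 4 | 8 / 6 / 6% | 80 / 83 / 83% |
| 0.02 | 1 / 2 / 4 | 11 / 8 / 6% | 75 / 79 / 82% |
| 0.05 | 1 / 2 / 4 | 21 / 12 / 8% | 60 / 72 / 79% |
| 0.10 | 1 / 2 / 4 | 37 / 20 / 11% | 43 / 62 / 74% |

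**Step 4: weaker clustering.** If only MT and SHD + MT cluster, false positives at ICC 0.05 are about 15 / 10 / 7%. If those two arms shared two training classes, the figure is about 10%, or 8% with the diet arm unclustered.

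**Step 5: the planned test itself.** At f = 0.40 and ICC 0.01 to 0.05, the unadjusted ANOVA still rejects in about 85% of simulations. Its direct fault is false positives. The power loss appears only when the test is made to keep 5%.

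**Step 6: can the class variance be estimated?** At ICC 0.05 with three clustered arms, the class-variance estimate is zero in about 42% of datasets with two classes per arm and 38% with four. In those datasets a mixed model collapses to the ordinary ANOVA.

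**The case against.** The strongest reply is that the size rests wholly on assumptions. The article gives no ICC and no class count, and nothing in it supports 0.05 for laboratory-measured blood markers. This stands, and it limits three tempting inferences:

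- **That the stated 80% power is not delivered.** The documents do not support this. Power is roughly held at ICC 0.01 and, with small classes, at 0.02. As Step 5 shows, the planned ANOVA itself does not lose power.
- **That the false-positive rate is about 21%.** That figure needs ICC 0.05, one class per arm and equal clustering in all three active arms. Diet has only three group sessions plus individual parts, so its clustering is probably weaker.
- **That classes are nested within arms.** The article does not say so. SHD + MT received the same programmes as the single arms, and the Discussion refers to one intervention location for all, although 2.1 calls the study multicentre. If MT and SHD + MT trained together, the cap rules out a single class for about 40 people.

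A simple random effect is also no complete remedy. It cannot be estimated with one class per arm, it is unstable with two, and one term cannot represent participants who belong to both a training class and a nutrition group.

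A further reply is that an article leaves such detail to the full protocol or analysis plan. That would answer a complaint about mere silence. Here the article commits to a power basis, a model and a set of covariates, and the error structure they imply does not fit the delivery it describes. Data collection has ended (2.1), so the sample cannot change, but 2.6.1 and 2.7 describe the biomarker analyses as still to come.

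**Conclusion.** The point holds in limited form. Group delivery and an independence-based sample size and analysis are both on the page, and any positive class correlation makes the planned intervals too narrow and the group-by-time test too liberal. With 20 analysed per arm and all three active arms clustered, the per-test false-positive rate is about 6-8% at ICC 0.01 and 8-21% at ICC 0.05. If only the exercise arms cluster, it is about 7-15% at 0.05. The 80% power is not assured for a test that keeps 5%: an upper bound is 80-83% at ICC 0.01 and 60-79% at ICC 0.05. Every one of these figures depends on an ICC and a class structure that the article does not give. The direction of the error is certain if classmates correlate at all; its size is not. It is worth correcting before the biomarkers are analysed.

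**What to change.** **In 2.7:**
- Report the number of training classes and nutrition groups per arm, and whether arms shared them.
- Where there are several classes, analyse each biomarker's change with a mixed model. Include a random effect for training class in the arms that trained in classes (crossed with arm if classes were shared), and one for nutrition group where membership is known. Treat controls as singletons and use small-sample degrees of freedom. SPSS, already named, fits such models.
- Where an arm had one or two classes, or the class variance is estimated as zero, state that class and arm effects cannot be reliably separated. Report a sensitivity analysis that multiplies standard errors in the clustered arms by √(1 + (m - 1) x ICC) for ICC 0.01 to 0.10.

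**In 2.3:** state that 80% power at 0.40 assumes no class clustering. Give a range over assumed ICCs, labelled as an upper bound because it treats the ICC as known.

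**Cost:** analysis wording and group membership for each participant, with no new participants or procedures. Training class should be recoverable from the attendance that 2.5.2 says was recorded. The article mentions no such record for the nutrition groups, so that term may not be possible. The downside is wider intervals and a less favourable power statement.
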